### Procedures to evaluate endpoints

By comparing the questionnaires we can evaluate the clinical endpoints. By examining the urine samples we can evaluate the bacteriological endpoints. By asking for a questionnaire on day 28 we can evaluate any relapse/reinfection, hospitalization or secondary consultation, and afterwards look in the collaborating department of clinical microbiology’s databases for urosepsis or pyelonephritis.

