#### Key exclusion criteria

Allergy to penicillins and cephalosporines.Clear signs of (i.e. high fever ≥38,5 °C or flank pain/tenderness) or high suspicion of pyelonephritis.Any condition that may lead or predispose to complicated urinary infection (i.e. indwelling urinary catheter, pregnancy, immunosuppressive therapy, abnormal urinary tracts, recurrent UTI, serious neurological disease affecting the bladder).Porphyria or systemic primary carnitine deficiency or of the type organic aciduria (i.e. methylmalonic aciduria and propionacid anemia).Symptoms correlating with differential diagnosis (i.e. vaginal discharge or pain).Ongoing/current antibiotic therapy.Oesophageal stricture.Current intake of allopurinol (i.e. increases the risk of allergic skin reaction to mecillinam) or probenecid (i.e. decrease the renal excretion of mecillinam) or valproate.Currently part of another clinical trial. Inability/unable to understand and/or take part in the clinical trial

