### Criteria for termination from the study

If a patient during the study would develop signs of upper UTI (i.e. pyelonephritis), treatment failure, serious adverse effects or allergic reactions to the medicine, or decision of withdrawal, she will have to terminate from the study and possibly get a new evaluation by a physician.

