### Second medical consultation

Patients will be told at recruitment to visit the GP again if she develops worsening of symptoms or not experiencing any symptom relief during the study period. In that case the GP is able to choose a new treatment strategy for the patient and will have the potential microbiological diagnostic answers (i.e. from pre-treatment urine sample) to take in consideration in this approach.

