### Secondary endpoints

Clinical signs and symptoms in uncomplicated LUTIs in women.Frequency and timing of relapse of symptoms and/or bacteriuria.Bacteriological findings (i.e. ESBL producing bacteria).Complications (i.e. urosepsis and/or pyelonephritis) within 28 days.

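### The only source named for identifying pyelonephritis and urosepsis within 28 days is a microbiology database, which can miss cases that the protocol elsewhere recognises by clinical signs

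*Protocol article*

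**What the plan says.** All references are to the protocol article.

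- **Secondary endpoints** lists "Complications (i.e. urosepsis and/or pyelonephritis) within 28 days".
- **Definitions**, under Outcome, defines clinical and bacteriological cure, relapse and reinfection. It defines neither complication.
- **Procedures to evaluate endpoints** describes two steps. First: "By asking for a questionnaire on day 28 we can evaluate any relapse/reinfection, hospitalization or secondary consultation". Then the investigators will "afterwards look in the collaborating department of clinical microbiology’s databases for urosepsis or pyelonephritis".
- **Key exclusion criteria** recognises pyelonephritis at entry by "Clear signs of (i.e. high fever ≥38,5 °C or flank pain/tenderness) or high suspicion of pyelonephritis".
- **Criteria for termination from the study** begins: "If a patient during the study would develop signs of upper UTI (i.e. pyelonephritis), treatment failure, serious adverse effects or allergic reactions to the medicine". Of a patient who meets a criterion it says that "she will have to terminate from the study and possibly get a new evaluation by a physician".
- **Second medical consultation** sends patients back to their doctor: "Patients will be told at recruitment to visit the GP again if she develops worsening of symptoms". The GP may then change treatment with the pre-treatment culture in hand. No new culture is mentioned.

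**The concern.** The article treats pyelonephritis as a clinical diagnosis when it screens patients and when it withdraws them, but looks for it in a laboratory source when it evaluates the endpoint. A culture result does not in itself show fever or flank pain. A case that a GP diagnoses and treats without sending a urine sample leaves no culture for the search to find.

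This is the only item among the listed endpoints that asks whether infection ascends or becomes systemic after treatment. The section on scientific and societal perspective foresees keeping the 3-day course if it proves non-inferior. A report of few or no complications would be read as support for that, so it should rest on all the cases that the trial itself came to know of.

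**Working it through.** **The article's own figures.** No figure is stated for the complication endpoint. The efficacy sample size does reproduce. With 90% versus 75%, two-sided 0.05, power 0.80 and a continuity correction, the two-proportion formula gives 113 per group. Then 113/0.7 = 161.4 and 161/0.7 = 230.0, matching 161 and 230. None of this bears on how complications are found. It only supplies the 230 per group used below.

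**Following a case through the text.** Suppose a woman develops fever and flank pain on day 6.

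1. She has been told to return if her symptoms worsen. The GP can choose new treatment using the day-0 culture. Nothing requires another sample, so the visit need not create a laboratory record.
2. Signs of upper urinary infection are a termination criterion, so she leaves the study. Whether a physician then evaluates her is left open.
3. The day-28 questionnaire is the step that would show a hospital stay or second consultation. Nothing says that she still receives it, or that she is contacted on days 28–30.
4. The database search comes last. If her only culture is the day-0 sample, the search shows the infection she entered with and no new event.

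The trial would know of this case from step 2, but the endpoint procedure does not name terminations as a source. Nor does it name second consultations as reported by the GP, the planned contacts (Follow-up), or serious-event reports (Adverse effects/risks). The section on data processing lists the source data as GP and patient questionnaires and laboratory answers. The only GP questionnaire that the article describes is the inclusion form.

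**Illustration of size, on assumed values only.** The documents give neither a complication risk nor a capture proportion. Let p be the true 28-day risk and s the share of cases that the database search finds, with 2 × 230 = 460 patients.

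- Expected cases = 460p
- Expected cases found = 460ps
- Chance that none is found in either arm = (1 − ps)^460

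| Assumed p | Expected cases | Found, s = 0.3 to 0.9 | Chance of finding none, s = 0.3 to 0.9 |
|---|---|---|---|
| 0.5% | 2.3 | 0.7 to 2.1 | 50% to 13% |
| 1% | 4.6 | 1.4 to 4.1 | 25% to 2% |
| 2% | 9.2 | 2.8 to 8.3 | 6% to 0.02% |

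With full capture (s = 1) the chance of no case at all is about 10%, 1% and 0.01% in the three rows. At the lower capture values, an observed count of zero is therefore much weaker evidence that no cases occurred. The table cannot say which row or which capture value applies here.

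**The case against.** The strongest reply is that the article contains no scoring rule. It does not say that a reported case without a culture is discarded. The questionnaire comes first and the database search follows, which can be read as a search added to reported events. This stands. A reader might infer that clinically diagnosed pyelonephritis would be scored as no complication, but the text does not go that far. It supports only that no clinical source is named for identifying the two conditions.

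Other parts of the reply also stand:

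- The clinical criterion in the exclusion list is fever **or** flank pain or tenderness, or high suspicion. It is an entry rule and not an outcome definition, so its difference from the endpoint source is a mismatch to reconcile and not a formal contradiction.
- A reader might also infer that positive study urines would be counted as pyelonephritis. That is speculative. Study urines have scheduled days, and significant growth at day 28 after bacteriological cure already has its own categories, relapse or reinfection.
- The content and coverage of the databases are not described, so missed cases are a possibility of unknown size.
- Patients, physicians and investigators are blinded. Incomplete capture applies to both arms, and there is no evident reason for it to favour one.
- Even with full capture the endpoint is close to descriptive. If 2 of 230 were compared with 7 of 230, Fisher's exact test gives p = 0.18; 1 against 4 gives p = 0.37. It would be wrong to say that losing two or three cases decides whether a signal is seen.

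The last argument is that a case definition may sit in the full protocol, which is not shown. That would excuse silence, but the article is not silent. It names a source, and the trial's own procedures already generate better ones.

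**Conclusion.** The point holds as a minor one. The only source named for identifying pyelonephritis and urosepsis can miss cases recognised clinically, above all in women terminated for signs of upper urinary infection who may not return the day-28 questionnaire. This rests on three things in the text: the wording of the endpoint procedure, the clinical recognition of pyelonephritis elsewhere, and the absence of any required culture at a second consultation. It also assumes that a culture record does not carry the clinical signs.

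The number of cases lost cannot be derived from the documents, and the table above is illustration only. The documents do not support saying that cases will be missed, that reported cases will be rejected, or that one arm will be favoured. The co-primary endpoints, their analysis and the sample size are unaffected.

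**What to change.** In the section on procedures to evaluate endpoints, reconcile the source with the exclusion and termination criteria:

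1. Count as a complication any physician-diagnosed or clinically recognised upper urinary infection, or urosepsis, from day 0 to day 28.
2. Name the sources: terminations for signs of upper urinary infection, second consultations, the planned contacts on days 9–11 and 28–30, the day-28 questionnaire, and serious-event reports.
3. Keep the database search as supporting evidence.
4. Continue data collection for this endpoint to day 28 in patients terminated from the study.
5. Classify cases while the data are still coded, which fits the plan to de-code only after the analysis.

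The cost is small: revised endpoint wording, a question at contacts that are already planned, and a day-28 contact for the few terminated patients. The downside is that some patient-reported events will need checking with the treating GP. No treatment rule needs to change.

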## Power, sample size and analysis

### Definitions

The intention-to-treat (ITT) analysis will be consisting of all included patients (i.e. patients that present with symptoms of uncomplicated LUTI and are included in the study). The per-protocol (PP) analysis will be consisting of all the patients that follow-up with clinical and bacteriological data (i.e. excluding the dropouts). The need-to-treat (NTT) analysis will be stratified from the PP analysis to only include patient with true uncomplicated LUTI (i.e. symptoms and significant bacteriuria, only isolates susceptible to mecillinam).

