#### Microbiological diagnostics

One pre-treatment urine sample (day 0) with optional urine-dipstick, and two control urine samples (day 8–10 and day 28–30, respectively) will be sampled from the patient. The three urine samples will be sent to the DCM, Hvidovre University Hospital, Denmark, for examination of the presence and count of uropathogenic bacteria. In presence of significant bacteriuria (i.e. ≥10^3^ bacteria/ml [*E. coli*] / ≥10^4^ bacteria/ml [other uropathogenic bacteria]) the isolates will also be examined for resistance mechanisms and patterns, minimal inhibitory concentration (MIC) to mecillinam (i.e. by E test, AB Biodisk, bioMe’rieux, Marcy-l’E’ toile, France) and determining the bacterial specimen (i.e. MALDI-TOF, Brukner, Germany). All urine samples will processed according to laboratory routine and susceptibility tested according to EUCAST guidelines [18]. During the study all significant uropathogenic isolates will be stored at minus 80 °C. At the end of the study these isolates will be genetically examined to determine their more specific identity/type, i.e. so we can evaluate if the potential relapse is either a true relapse or a reinfection (i.e. the same or different type of bacterial specimen).

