## Outcome

### Primary endpoint

We have two co-primary endpoints:
**Co-primary endpoint no. 1** –clinical efficacy (i.e. which group will be clinically cured fastest and proportion of patients cured at day four).
**Co-primary endpoint no. 2** – bacteriological efficacy (i.e. proportion of patients bacteriologically cured at first control urine sample).

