### Power analyze

We hypothesize that there is a 15% absolute differences in efficacy between the groups, measured in clinical efficacy. We believe there to be an even bigger difference in bacteriological efficacy. Assuming an efficacy of 90 and 75% for 5 days and 3 days therapy, respectively, using a double-sided test with *p* < 0.05, and a statistical power of 0.8, we will need 113 patients in each group for the NTT analysis. With an estimated fall-out rate of app. 30% between each arm; 161 patients per group will need to be included for the PP analysis, and 230 in each group for the ITT analysis. There is a possibility for an interim analysis after 300 included participants, since we cannot reject a possibility for a higher (i.e. 20%) absolute efficacy.

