## Data processing and statistical analysis

The source data is the GP’s and patient’s questionnaires and the diagnostics answers from the microbiological lab at the DCM. All source data will all be stored by the investigator and sponsor, in originals and scanned copies, at the DCM. The collected source data are transferred, logged and processed in the computers of the DCM. Analysis will be made in ITT, PP, and NTT form, respectively. All data will be analyzed coded, and only de-coded after the analysis is done and the analytic results are written in the relevant sections in the future article. The statistical software packages SAS (SAS Institute, Cary, NC) will be used for all analyses. Categorical data will be analyzed using a Fisher’s Exact test.

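### PP requires both clinical and bacteriological follow-up, and NTT is cut from PP, so in these two sets a woman can leave one co-primary comparison because data for the other are missing

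*Protocol article*

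**What the plan says.** All references are to the protocol article.

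- **Sets (Power, sample size and analysis, Definitions).** For ITT: "The intention-to-treat (ITT) analysis will be consisting of all included patients". PP consists of "all the patients that follow-up with clinical and bacteriological data (i.e. excluding the dropouts"). NTT is nested in PP: "The need-to-treat (NTT) analysis will be stratified from the PP analysis to only include patient with true uncomplicated LUTI", with the qualifying facts "symptoms and significant bacteriuria, only isolates susceptible to mecillinam".
- **Use of the sets (Data processing and statistical analysis).** "Analysis will be made in ITT, PP, and NTT form, respectively". No version of a set specific to one endpoint is given.
- **Power (Power analyze).** For 90% v 75%, two-sided 0.05 and power 0.8, "we will need 113 patients in each group for the NTT analysis". Two steps of about 30% fall-out lead to 161 for PP and 230 for ITT.
- **Endpoints (Primary endpoint; Procedures to evaluate endpoints).** The clinical co-primary is "which group will be clinically cured fastest and proportion of patients cured at day four", taken from questionnaires. The bacteriological co-primary is cure at the first control urine, taken from urine samples.
- **Urine sampling (Microbiological diagnostics).** "One pre-treatment urine sample (day 0) with optional urine-dipstick, and two control urine samples (day 8–10 and day 28–30, respectively").
- **Termination (Criteria for termination from the study).** Treatment failure is one of the listed reasons for leaving the study.

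**The concern.** The two co-primary endpoints rest on different observations, yet one membership rule asks for both kinds. A woman with a full symptom diary and no control culture is left out of the PP and NTT clinical comparison, although her clinical outcome is known. A woman with a control culture and no diary is left out of the bacteriological one.

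The loss need not be random. A woman terminated for treatment failure who then gives no control urine has a known clinical failure, but the rule removes her from the clinical comparison. The plan expects 25% failures on 3 days and 10% on 5 days, so this can act unequally on the arms.

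NTT does not need this condition. Its criteria are symptoms, significant bacteriuria and susceptibility. Symptoms are scored at inclusion, and the urine that qualifies a woman is the pre-treatment one. NTT could be drawn from all included women, but it inherits the follow-up requirement through PP. It matters because NTT carries the power claim.

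**Working it through.** **1. The plan's own sizes.** Inputs from Power analyze: p1 = 0.90, p2 = 0.75, two-sided 0.05 (z = 1.960), power 0.8 (z = 0.842), mean p = 0.825.

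- Uncorrected: n = [1.960 × √(2 × 0.825 × 0.175) + 0.842 × √(0.90 × 0.10 + 0.75 × 0.25)]² / 0.15² = 99.5.
- With continuity correction: (99.5/4) × [1 + √(1 + 4/(99.5 × 0.15))]² = 112.5, that is 113. This matches.
- 113/0.7 = 161.4 and 161/0.7 = 230. These match the 161 and 230.
- Exact power of Fisher's test (the test named for categorical data) at 113 per arm, by full enumeration: 81.7%.

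The plan's order is therefore ITT 230, less dropouts, PP 161, less women without true LUTI, NTT 113.

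**2. What each part of the rule needs.**

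| Item | Data needed | Source |
|---|---|---|
| Clinical co-primary | symptom record | questionnaires |
| Bacteriological co-primary | first control urine, day 8–10 | urine sample |
| NTT status | symptoms, bacteriuria, susceptibility | inclusion visit and day-0 urine |
| PP membership, hence NTT | clinical and bacteriological follow-up | both |

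No endpoint needs everything in the last row, and NTT status needs none of it. The Definitions section does not itself say day 0 for the bacteriuria. That reading comes from Inclusion criteria, where bacteriuria belongs to the definition of LUTI, and from Microbiological diagnostics, where one sample precedes treatment.

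**3. How many could be regained.** Assume that NTT status is independent of dropout, so that the plan's second 30% step applies to all included women. Then 230 × 0.7 = 161 per arm meet the NTT criteria. The plan keeps 113, so 161 − 113 = 48 per arm are lost through the follow-up condition. How many of the 48 hold the outcome being analysed is not given, so a range is shown (90% v 75%, exact Fisher):

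| Regained of 48 | Analysed per arm | Power |
|---|---|---|
| 0 | 113 | 81.7% |
| 5 | 118 | 83.2% |
| 16 (1/3) | 129 | 86.8% |
| 24 (1/2) | 137 | 89.1% |
| 32 (2/3) | 145 | 90.7% |

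The Questionnaires section says that the patients' questionnaires are submitted together with the urine samples. The two outcomes will then often be missing together, which favours the upper rows of the table.

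**4. Illustration of selection (retention rates are assumed).** Suppose 75% of cured and 60% of failed women are kept.

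- 5 days: kept 0.90 × 0.75 + 0.10 × 0.60 = 0.735; apparent cure 0.675/0.735 = 91.8%.
- 3 days: kept 0.75 × 0.75 + 0.25 × 0.60 = 0.7125; apparent cure 0.5625/0.7125 = 78.9%.

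The difference falls from 15.0 to 12.9 points, while overall retention stays near the plan's 70%. The true retention pattern is unknown, so this shows that a distortion is possible, not how large it is.

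**The case against.** The case on the other side has several parts.

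- **Outcomes are not lost to the trial.** A reader might infer that observed co-primary outcomes are thrown away. They are not: ITT keeps all included women and is one of the three stated analyses. This stands and confines the point to PP and NTT.
- **The gain may be close to nothing.** A reader might take 87% to 91% power as the expected benefit. Joint return of questionnaires and urine speaks against that. This stands in large part. Partial data remain possible, because the Follow-up section provides calls or texts about questionnaires and samples, and a clinical failure can be known without a culture.
- **The sizes were planned for these sets.** This stands: 113/161/230 reproduce, and power at 113 exceeds 0.8. The point is about who is analysed, not about an arithmetic error.
- **The reading is not forced.** PP is glossed as excluding dropouts, and a woman with a diary but no urine is not plainly a dropout. Applying the rule to both endpoints is an inference, and a fuller protocol or analysis plan might define evaluability per endpoint. This stands only in part: the article states the requirement for both kinds of data, offers no other set, and a later document would have to override it.
- **Per-endpoint evaluability still excludes women after randomisation.** This stands. The remedy reduces the selection but does not remove it.

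**Conclusion.** The point holds for PP and NTT. As defined, they drop women from one co-primary comparison because the other co-primary's data are missing, and NTT, the powered set, is conditioned on follow-up that its own criteria do not need. The main harm is selection after randomisation that may depend on outcome and differ by arm; its size and direction cannot be established from the document.

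The loss in numbers is between 0 and 48 per arm, given independence of NTT status and dropout. It is probably toward the low end: 0 or 5 regained gives 81.7% or 83.2% power. The documents do not support the stronger readings that the stated sample size is wrong, that outcomes are lost to every analysis, or that a large gain in power is available. The definitions should be corrected because the change is cheap and the affected set carries the power claim.

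**What to change.** Change the set definitions in two places.

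1. Define NTT from all included women by symptoms at inclusion, significant bacteriuria in the day-0 urine and mecillinam susceptibility of that isolate.
2. In PP and NTT, require for each co-primary endpoint only its own data. For the clinical endpoint these are the diary data for both time to cure and cure at day 4, with documented treatment failure counted as known clinical status. For the bacteriological endpoint it is the first control urine.

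Keep the set with both outcomes available as a sensitivity analysis, and keep 113 per arm as the minimum size. The cost is about two sentences and one extra table, with no additional patients. The downside is that the two endpoints will have different denominators. Women missing the endpoint's own data remain excluded, so the PP and NTT results should still be read with that in mind.
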